**Figure 5 F5:**
[figure not shown]
Study schema outlining recruitment, data collection and data analysis.

### Sample size

A sample size of 4000 women was determined after taking into account the number of births at study sites, inclusion and exclusion criteria, and a prevalence of around 11.5% of the events of interest (hypertensive disease in pregnancy, SGA or FGR, gestational diabetes) within the study cohort. Additionally, a sample size of 4000 would allow sensitivity of the Salurate algorithm to identify any of the events of interest with a 95% CI to within plus or minus 5% of the point estimate if sensitivity is found to be around 50%, improving to plus or minus 3% at a higher sensitivity of 90%. Specificity will be estimated to a much higher degree of precision because the proportion of participants that will not encounter adverse outcomes is expected to be much larger.

### Inclusion and exclusion criteria

All women aged 16 years old and over with a viable singleton intrauterine pregnancy between 10 and 16 weeks’ gestation at the time of enrolment, a risk of preterm pre-eclampsia of >1:300 as determined by the Aspirin for Evidence-Based Pre-eclampsia Prevention algorithm^5^ and able to provide informed consent will be eligible for recruitment. The algorithm combines maternal factors, mean arterial pressure (MAP), uterine artery pulsatility index (UtA-PI) and maternal serum pregnancy-associated plasma protein-A (PAPP-A) and PlGF at 11–13 weeks’ gestation and is used routinely at recruiting centres. Exclusion criteria: significant comorbidities that will interfere with participation or physical incapacitation from performing self-sampling; presence of serious mental illness, learning disabilities or educational status or language barrier that influences capacity to use the Salurate app or understand the instructions for use; lack of access to a smartphone or internet at home; periodontal disease, gingivitis or oral cancer.

### Schedule of events

Participants will be approached at their initial visit, and subject to eligibility and consent, will be enrolled in the study. They will be issued a Salurate sampling kit, and a member of the research team will guide the participant through the process of taking a sample and using the Salurate app to upload a picture of their test. Their unique study ID will be registered on the Salurate Clinician Portal and an initial CRF will be completed, recording data on maternal demographics, medical history, obstetric history and data from their first trimester combined pre-eclampsia screening (MAP, PAPP-A, crown-rump length, left and right UtA-PI and risk of preterm pre-eclampsia).

Each participant will submit weekly samples from enrolment until the conclusion of pregnancy. A predictive model algorithm analyses the data supplied by the participants via the Salurate app and provides a prediction with the likelihood of an adverse event (hypertensive disease of pregnancy, FGR) occurring. Several colourimetric measurements are extracted from the uploaded test from the participants, which relate to the concentration of uric acid in the saliva sample. The algorithm looks at the change from week to week, and using the trend from preceding weeks calculates a risk of HDP within a given timeframe. The trend is based on specific patterns of uric acid levels linked with known HDP events learnt from previous trials data. This prediction is calculated post hoc and not revealed to the participant or clinical trial research team. Data on the primary and secondary outcomes will be retrieved from the participants’ medical notes at the conclusion of pregnancy and added to the CRF.

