### Salurate system

Salurate is a non-invasive, home-use self-sampling system. A saliva sample is applied to colourimetric test paper (encapsulated in a test cartridge). An enzymatic reaction occurs, which produces a purple colour of varying intensities. The intensity of the colour change is directly proportional to the salivary uric acid concentration. While the colour change on the test paper may be visible to the naked eye, accurately interpreting the results is not possible through visual observation alone. The Salurate prediction algorithm employs advanced image analysis techniques to evaluate images submitted over the past few weeks before generating a prediction (figure 1).

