### Outcomes

The study’s primary outcome is the incidence of hypertensive disease of pregnancy. This is defined as any of the following:

Gestational hypertension.Pre-eclampsia.Eclampsia.Haemolysis, elevated liver enzymes, low platelets syndrome.Chronic hypertension with superimposed pre-eclampsia.^18^

Diagnostic criteria are specified in online supplemental material.

Secondary outcomes: SGA (birth weight less than 10th percentile for that gestational age, or 2 SD below the population mean on growth charts); FGR (SGA or birth weight below expected for trajectory of growth with evidence of placental insufficiency)^19^; GDM (any degree of glucose intolerance with onset or first recognition during second or third trimester of pregnancy); sPTB; stillbirth; sampling adherence (frequency of missed samples, dropout rate). Centiles will be determined using Intergrowth references.^20^

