### Data analysis

The quantitative data for this study will be analysed and reported according to the relevant reporting guidelines.^16 21^ All analyses will be performed in StataSE V.16.1 statistical analysis software. All clinical primary and secondary outcomes (maternal and neonatal) will be presented across the whole cohort as percentages with 95% CIs. Missing outcomes data will be presented. Women’s characteristics at enrolment into the study will also be presented with percentages or summary statistics as appropriate.

Salivary uric acid concentration (Salurate) observations will be presented graphically over time from the initial 10–14 weeks pregnancy record through to the end of study participation (1) for the whole cohort, (2) by primary outcome (HDP present or absent) and (3) for each secondary outcome, including adverse maternal or perinatal outcomes. Numbers and percentages of missing Salurate reports will be presented by week of pregnancy with the number of women participating in the study as the denominator (which may vary in the last weeks of the study depending on when they give birth). This will be used to assess the degree of compliance of women to the testing regimen. No multiple imputation or other forms of missing data replacement will be used to estimate missing values of Salurate. No missing data replacement will be employed for clinical outcomes or participant’s characteristics at enrolment, and every effort will be made to record these data. We anticipate that rates of data missingness will be low.

A mixed-methods analysis of longitudinal data will be used to determine the relationship between Salurate results and the primary and secondary outcomes in this cohort. The Salurate algorithm will be employed, and its sensitivity, specificity, PPV and NPV to identify the primary outcome will be presented with 95% CIs. We will also determine how soon the primary outcome would be indicated using Salurate results and compare this with traditional prediction methods such as the FMF algorithm or National Institute for Health and Care Excellence (NICE) checklist. Subgroup analyses will explore whether the Salurate algorithm has greater diagnostic value in particular women according to baseline characteristics, although these analyses may not have enough statistical power to be definitive.

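### Samples taken after HDP diagnosis are not kept out of the accuracy analysis, and a time-limited prediction is scored against HDP with no time limit

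*Protocol article*

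**What the plan says.** All references are to the protocol article.

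- **Sampling (Schedule of events):** "Each participant will submit weekly samples from enrolment until the conclusion of pregnancy". No stop or cut-off at HDP diagnosis is given.
- **Index test (Schedule of events; Salurate system):** the algorithm, "using the trend from preceding weeks calculates a risk of HDP within a given timeframe". The length of that timeframe is not given. The algorithm is said to "evaluate images submitted over the past few weeks before generating a prediction".
- **Timing of the prediction (Schedule of events):** "This prediction is calculated post hoc and not revealed to the participant or clinical trial research team".
- **Target (Outcomes):** the "primary outcome is the incidence of hypertensive disease of pregnancy", defined by any of five diagnoses, with no time window.
- **Accuracy (Data analysis):** "The Salurate algorithm will be employed, and its sensitivity, specificity, PPV and NPV to identify the primary outcome will be presented with 95% CIs".
- **Curves (Data analysis):** Salurate values are plotted over time, including by whether HDP occurred, "through to the end of study participation". A longitudinal analysis relating Salurate results to outcomes is also planned, with no cut at diagnosis.
- **Intent (Objectives; Data analysis):** the aim is to identify women who later develop HDP. A separate analysis asks how early Salurate would have indicated it, compared with existing prediction methods.

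**The concern.** Two features of the text do not fit the aim of prediction.

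First, a woman diagnosed some weeks before delivery continues to submit samples. Predictions are computed afterwards from the stored images, and nothing stated stops the algorithm from using the later ones. A positive result that arises only after diagnosis is detection, yet it could turn a missed case into a true positive. The same samples would widen the gap between the HDP and non-HDP curves, and the association in the longitudinal analysis.

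Second, the algorithm gives a risk over a limited period, but the outcome it is scored against has no limit. How a prediction is classified then depends on something the algorithm did not claim. A positive whose horizon has long passed can count as correct because HDP appears near term. If individual predictions are scored, a correct short-horizon negative can count as wrong for the same reason.

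What is at stake is the headline result: sensitivity, specificity, PPV and NPV for HDP.

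**Working it through.** **1. The plan's own figure.** Sample size gives 4000 women, an 11.5% prevalence of the events of interest (a composite wider than HDP), and 95% CI half-widths of 5 points at 50% sensitivity and 3 points at 90%.

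- Events: 4000 × 0.115 = 460.
- Half-width = 1.96 × √(p(1 − p)/460).
- p = 0.5: 4.57 points. p = 0.9: 2.74 points.

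These round to the stated 5 and 3. The calculation uses one result per affected woman, which supports reading the planned accuracy analysis as one score per woman. That is an inference from the figures, not a stated rule.

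**2. The passages side by side.**

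| Element | Time frame as stated |
|---|---|
| Samples | Enrolment to end of pregnancy |
| Algorithm output | Risk of HDP within an unspecified period |
| Outcome scored against | HDP, no period |
| Curves by HDP status | To end of participation |
| Stated aim | HDP that has not yet developed |

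The last row requires a cut at diagnosis. None of the rows above it contains one. Rows two and three differ in time frame.

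**3. Illustration of post-diagnosis samples.** No input here is in the document. Let s be the true sensitivity from pre-diagnosis samples, k the number of later samples and q the weekly alert rate after diagnosis. Assume independence between weeks, and that a later alert makes the woman positive.

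- Apparent sensitivity = s + (1 − s)(1 − (1 − q)^k).
- s = 0.5, k = 3, q = 0.1: 0.5 + 0.5 × (1 − 0.9³) = 0.5 + 0.5 × 0.271 = 0.636.
- s = 0.5, k = 3, q = 0.3: 0.5 + 0.5 × (1 − 0.7³) = 0.5 + 0.5 × 0.657 = 0.829.

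**4. Repeated looks, conditional on a rule the document does not state.** Suppose any positive week made a woman positive. Enrolment at 10 to 16 weeks (Inclusion and exclusion criteria) and an assumed delivery at 37 to 40 weeks give between 37 − 16 + 1 = 22 and 40 − 10 + 1 = 31 samples. If each prediction needs three earlier weeks, that leaves 19 to 28 predictions. Take 25 looks and an assumed weekly specificity of 95%.

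- Independent looks: 1 − 0.95²⁵ = 72% of unaffected women flagged.
- Simulated first-order autoregressive correlation of 0.5, 0.8, 0.9, 0.95: 62%, 43%, 30%, 22%.
- Simulated exchangeable correlation of 0.5, 0.8, 0.9, 0.95: 37%, 21%, 14%, 11%.

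The range is therefore about 11% to 72%, against 5% for a single week.

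**The case against.** The strongest reply is that much of this is silence rather than error. The horizon, the positivity threshold, the rule giving one result per woman and the handling of samples after diagnosis may all sit in the full protocol or the statistical analysis plan, neither of which is shown. The objectives plainly concern future HDP, a lead-time analysis is planned, and the curves are descriptive.

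Part of this stands. The absence of a threshold or of a woman-level rule is not itself a finding. A reader might also infer three stronger things that the document does not support:

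- **That about 25 weekly looks will inflate both sensitivity and false positives.** The article states weekly samples. It does not state a number of predictions per woman or that any positive week counts. Under such a rule sensitivity and false positives would rise together, both would be reported, and they would still describe that rule. Nor can this be added to the misclassified early negative as if both applied: the latter needs each prediction scored separately, the former one score per woman.
- **That the study cannot show identification weeks ahead.** The lead-time analysis addresses that question directly.
- **That accuracy at fixed gestations must become primary.** That is one sound design among several, and it would displace the one-result-per-woman basis of the sample size.

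What does not stand is that intent settles the matter. The article states a sampling end and a plotting end beyond diagnosis, and an outcome without a window beside a test with one. The lead-time analysis is additional and does not restrict which samples enter sensitivity or specificity.

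**Conclusion.** The point holds in a limited form. Followed as written, the plan allows post-diagnosis samples into the curves, the longitudinal analysis and the accuracy estimates, and compares a time-limited prediction with an outcome that has no time limit. The first would tend to raise apparent sensitivity. The second means that the estimates need not describe accuracy over the period to which the algorithm refers.

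The size is unknown. The move from 50% to 64% (or 83% at a 30% weekly alert rate) rests wholly on assumed sensitivity, alert rates, number of later samples and independence. The 11% to 72% false-positive range applies only if any positive week counts. Neither should be quoted as an expected bias in this study.

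**What to change.** In Data analysis, state that:

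1. For women with HDP, only samples taken before the date of diagnosis enter the accuracy analysis, the longitudinal model and the curves by outcome.
2. The one-result-per-woman accuracy estimate is kept, counts only pre-diagnosis predictions, and uses the same rule for a positive result in sensitivity and in specificity.
3. A supporting analysis reports accuracy among women still pregnant and free of HDP at chosen gestations, scored against HDP within the algorithm's own horizon, with that horizon stated.

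Recruitment, sampling and care are unchanged, and predictions are already computed afterwards and withheld. The date of HDP diagnosis must be available from the notes, which the lead-time analysis needs in any case. The price is slightly lower apparent sensitivity, and wider intervals in the supporting analysis because each gestation has fewer events.

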### Outcomes

The study’s primary outcome is the incidence of hypertensive disease of pregnancy. This is defined as any of the following:

Gestational hypertension.Pre-eclampsia.Eclampsia.Haemolysis, elevated liver enzymes, low platelets syndrome.Chronic hypertension with superimposed pre-eclampsia.^18^

Diagnostic criteria are specified in online supplemental material.

Secondary outcomes: SGA (birth weight less than 10th percentile for that gestational age, or 2 SD below the population mean on growth charts); FGR (SGA or birth weight below expected for trajectory of growth with evidence of placental insufficiency)^19^; GDM (any degree of glucose intolerance with onset or first recognition during second or third trimester of pregnancy); sPTB; stillbirth; sampling adherence (frequency of missed samples, dropout rate). Centiles will be determined using Intergrowth references.^20^

### Monitoring

A trial steering committee, comprising an independent chair, chief investigator and lay person stakeholder, will meet at a minimum biannually to discuss trial monitoring. Adverse events and protocol deviations will be reported to the local research team and to the trial sponsors. Protocol amendments will be communicated to all relevant parties.

### Health economics analysis plan

Health economics analysis will be performed by Health Tech Enterprise (HTE) Company Registration Number 5285665. HTE will perform a scoping review, conduct interviews with obstetricians, parameterise the decision analytical model and evaluate the health economic impact of the intervention by assessing the incremental changes as compared against the current care pathway for the categorisation and treatment of patients at risk of pre-eclampsia.

### Data analysis

The quantitative data for this study will be analysed and reported according to the relevant reporting guidelines.^16 21^ All analyses will be performed in StataSE V.16.1 statistical analysis software. All clinical primary and secondary outcomes (maternal and neonatal) will be presented across the whole cohort as percentages with 95% CIs. Missing outcomes data will be presented. Women’s characteristics at enrolment into the study will also be presented with percentages or summary statistics as appropriate.

Salivary uric acid concentration (Salurate) observations will be presented graphically over time from the initial 10–14 weeks pregnancy record through to the end of study participation (1) for the whole cohort, (2) by primary outcome (HDP present or absent) and (3) for each secondary outcome, including adverse maternal or perinatal outcomes. Numbers and percentages of missing Salurate reports will be presented by week of pregnancy with the number of women participating in the study as the denominator (which may vary in the last weeks of the study depending on when they give birth). This will be used to assess the degree of compliance of women to the testing regimen. No multiple imputation or other forms of missing data replacement will be used to estimate missing values of Salurate. No missing data replacement will be employed for clinical outcomes or participant’s characteristics at enrolment, and every effort will be made to record these data. We anticipate that rates of data missingness will be low.

A mixed-methods analysis of longitudinal data will be used to determine the relationship between Salurate results and the primary and secondary outcomes in this cohort. The Salurate algorithm will be employed, and its sensitivity, specificity, PPV and NPV to identify the primary outcome will be presented with 95% CIs. We will also determine how soon the primary outcome would be indicated using Salurate results and compare this with traditional prediction methods such as the FMF algorithm or National Institute for Health and Care Excellence (NICE) checklist. Subgroup analyses will explore whether the Salurate algorithm has greater diagnostic value in particular women according to baseline characteristics, although these analyses may not have enough statistical power to be definitive.

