**Methods and analysis:**

This is a prospective, multicentre, observational, cohort study with health economics evaluation. Women aged 16 and above, with a viable singleton pregnancy at <16 weeks gestation and a combined first trimester pre-eclampsia risk of >1:300 will be eligible for recruitment. Participants will perform weekly remote salivary uric acid testing from enrolment until the conclusion of pregnancy and upload results of colourimetric paper tests via a smartphone application. We will validate a predictive algorithm that analyses colour data from several consecutive samples to detect patterns that predict whether HDP is likely to occur. The primary outcome is test performance for the prediction of HDP. Secondary outcomes include adherence to sampling and test performance for predicting gestational diabetes, stillbirth and fetal growth restriction. Data on pregnancy outcomes will be collected from the medical notes, compared with the predictions made by the algorithm and subjected to statistical analysis.

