**Protocol version:**

4, 4 July 2024.

STRENGTHS AND LIMITATIONS OF THIS STUDYThis is a large, multicentre study which aims to include participants from a broad range of ethnicities and socioeconomic backgrounds.The secondary outcomes will allow us to assess if salivary uric acid could also be used as a predictor of related placentally mediated adverse pregnancy outcomes.The potential for inadequate assessment of specificity or sensitivity of salivary uric acid for hypertensive disorders of pregnancy is mitigated by employing a large sample size.Possible poor compliance with a weekly testing regime will be partly mitigated by reminders through a customised mobile application and opportunities to make up missed tests.

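### Salurate accuracy would most naturally cover only women with a usable prediction; state the denominator and add an all-enrolled analysis that scores no prediction as no alert

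*Protocol article*

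**What the plan says.** The Data analysis section of the protocol article rules out filling in missing test results: "No multiple imputation or other forms of missing data replacement will be used to estimate missing values of Salurate". It applies the same rule to clinical outcomes and baseline characteristics, and anticipates little missing data. Missing Salurate reports are to be counted by week of pregnancy, as a measure of compliance. The four accuracy measures for the primary outcome are then promised with 95% confidence intervals. No denominator is given.

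The Abstract says that the algorithm "analyses colour data from several consecutive samples to detect patterns". The Salurate system and Schedule of events sections agree: a prediction draws on images from the past few weeks and on the trend over preceding weeks, and gives a risk within a given timeframe. Predictions are calculated post hoc. None of these places gives a minimum number of samples or a rule for gaps.

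The strengths and limitations box accepts that "poor compliance with a weekly testing regime will be partly mitigated by reminders", and adds that missed tests can be made up. Adherence, including dropout, is a secondary outcome.

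The Objectives section asks how well the remote self-monitoring system predicts HDP. The Primary objective asks about including that system in women's care pathway.

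**The concern.** Taken together, these statements leave some women without a place in the analysis. A woman who lacks the samples the algorithm needs has no prediction, and no missing value will be replaced to create one. Unless a rule puts her somewhere, she falls outside the two-by-two table.

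For the question of how well the chemistry and algorithm work once a prediction exists, that may be acceptable. For the stated question about the system in the care pathway it is not. An HDP case for whom the system produced no prediction was not alerted, and dropping her removes a miss from the denominator of sensitivity.

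The planned reporting would not reveal this. A count of missing reports by week does not show how many individual women had no prediction, or whether they were more often HDP cases.

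**Working it through.** **1. The plan's own precision figure.** Inputs from the Sample size section: 4000 women and "a prevalence of around 11.5% of the events of interest", a composite of HDP, SGA or FGR, and gestational diabetes. Stated 95% CI half-widths are 5 points at 50% sensitivity and 3 points at 90%.

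- Events: 4000 × 0.115 = 460.
- Half-width = 1.96 × √(p(1 − p)/n).
- p = 0.50: 1.96 × √(0.25/460) = 4.57 points.
- p = 0.90: 1.96 × √(0.09/460) = 2.74 points.

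These round to the stated 5 and 3. All 460 events are used, so every event is assumed to have a usable prediction.

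**2. Loss of precision if women without a prediction are left out.** Let d be the share of event women without one. The article gives no value, so d is assumed.

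| d | Evaluable events | Half-width at 50% | Half-width at 90% |
|---|---|---|---|
| 10% | 414 | 4.82 | 2.89 |
| 20% | 368 | 5.11 | 3.07 |
| 30% | 322 | 5.46 | 3.28 |

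Both stated half-widths need 1.96² × 0.25/0.05² = 1.96² × 0.09/0.03² ≈ 384.1 events. They fail once d exceeds 1 − 384.1/460 ≈ 16.5%. The loss of precision is modest.

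**3. Share of all cases alerted.** A case with no prediction is not alerted, so:

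share alerted = sensitivity among evaluable cases × (1 − d).

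| d | Reported 90% | Reported 50% |
|---|---|---|
| 10% | 81% | 45% |
| 20% | 72% | 40% |
| 30% | 63% | 35% |

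**4. Intrinsic accuracy.** If the question is instead what the test would have shown had these women sampled, they might all have been missed or all detected. The bounds run from S(1 − d) to S(1 − d) + d. For a reported 90% they are 81–91%, 72–92% and 63–93% at d = 10%, 20% and 30%. The sign of any bias is open.

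**5. How easily a woman loses her prediction.** As an illustration, assume independent weekly misses, a required run of four weeks, and 24 weeks of sampling. None of these is stated in the article.

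- With 20% of weeks missed, a given four-week window is complete with probability 0.8⁴ = 41%.
- The chance of never having a complete four-week run is only 0.8% with 20% of weeks missed, 6.1% with 30% and 45% with 50%.

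Scattered misses rarely remove a woman altogether, but they often leave a particular window incomplete. That matters because the prediction concerns a given timeframe.

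**The case against.** Exclusion is inferred. The article does not say that women without a prediction leave the accuracy analysis, and its no-replacement rule is compatible with scoring them as not alerted, since that imputes no uric acid value. The full protocol or analysis plan may define the denominator. This stands, and it limits the point to what the text most naturally implies.

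A reader might infer that accuracy will be reported only for good compliers. The documents do not support that. A woman who misses some weeks can have another usable run, missed tests can be made up, no minimum number of samples is given, and little missing data is anticipated.

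A reader might also infer that declining to impute is itself the error, or that the test's intrinsic sensitivity is bound to be overstated. Neither follows. Not imputing an index test is defensible, and the bounds in step 4 of the working lie on both sides of the reported value. Outcome-related missingness is plausible but not documented; women who stop sampling once HDP appears still have the earlier samples that prediction uses.

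Nor does the Health economics analysis plan say which sensitivity enters the model, so no error there is shown.

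What the objection does not remove is the gap in reporting. Adherence by week says nothing about HDP cases without a prediction, and for the share of cases alerted the direction is fixed by arithmetic.

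**Conclusion.** The point holds for the system-level objective. With replacement ruled out and prediction dependent on consecutive samples, the natural reading is accuracy among women with a usable prediction. Under that reading, the sensitivity reported can equal or exceed the share of all HDP cases alerted, and cannot fall below it. The gap is the reported sensitivity multiplied by the share of cases without a prediction: 9, 18 or 27 points at a reported 90%, if that share is 10%, 20% or 30%. Those shares are assumptions. If missingness is as low as the article anticipates, the gap will be small, but the planned tables would not let a reader confirm it. For intrinsic accuracy no direction of bias is established. The change is worth making because it costs almost nothing and settles which question the headline figure answers.

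**What to change.** Keep the no-imputation rule for uric acid values, and add the following:

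1. Define a usable prediction (number of samples, permitted gaps, timing relative to the prediction window) before any predictions are generated. This matters because they are calculated post hoc.
2. Report the number and percentage of women without a usable prediction, separately for HDP and non-HDP women.
3. Report sensitivity, specificity, PPV and NPV (a) among women with a usable prediction and (b) over all enrolled women with a known outcome, with no prediction scored as no alert.
4. Base statements about the system's performance on (b), and statements about the test's intrinsic accuracy on (a).

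The cost is one extra table from data already collected, with no change for participants. Sensitivity will be lower under (b) whenever any HDP case lacks a prediction. Specificity under (b) is raised by construction: if d₀ is the share of non-cases without a prediction, it equals specificity among evaluable women × (1 − d₀) + d₀. With an assumed 90% and d₀ = 20%, that is 0.90 × 0.80 + 0.20 = 92%. Both analyses must therefore be shown side by side.
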